The laboratory will aim to report HPV results (i.e. authorised report released to NHAIS) within 5 days of receiving a self-sample. Once an authorised report has been successfully released into NHAIS, the relevant results letter will be triggered for release within the NHAIS system (further details below in the following section). Women should receive their results letter within two weeks of returning a self-sample (as per current NHSCSP guidelines).

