As an additional safety-net, when the trial reaches the end of recruitment, all self-sample screen positive women who have not attended for a follow up test will be highlighted to their GP practices who will make one further attempt to contact the women to come for a follow up test. This will be either by telephone call or text message as per GP Practice local procedures. Relevant women will be identified by the participating GP practices (designated trial administrator) using a pre-written search of the GP records or by the laboratory.

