### **7.5.3 Unavailable due to insufficient DNA**

Women who return a sample that has insufficient DNA (i.e. human beta globin not detected) to produce a viable result will be asked to repeat the self-sample in their results letter sent by CSAS. This will trigger a repeat kit to be made available to them within approximately 1 week of their results letter being sent. Based on a previous study we expect this to be rare (2%).(16)

If the repeat self-sample is also unavailable due to insufficient DNA, women will be advised (in their results letter sent by CSAS) to attend their GP practice for a conventional cervical screening test (collected by a nurse or doctor). This approach has been chosen because women who return a repeat kit indicates that they are highly motivated to be screened. There are no clinical safety concerns as two consecutive unavailable due to insufficient DNA results on a self-sample indicates poor sample-taking, not higher risk of having cervical abnormalities.

Unavailable results due to insufficient DNA will not elicit an action in NHAIS and their NTDD will remain unchanged.

As with women testing HPV positive, women who have an unavailable test result (due to insufficient DNA) will be safety-netted at their GP practice. A pre-written search of EMIS web (electronic patient record software) will identify all women with an unavailable self-sample result who either do not return a repeat (2nd sample) or who test unavailable on two consecutive samples. GP practices will be asked to contact these women (by letter, telephone call or text message) to invite them to come for a conventional screening test.

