### **7.6.3.2 HPV Testing and Result Reporting**

Valid samples will be tested for HPV using the Roche cobas® 4800 platform detailed further in Section Roche cobas 4800 System8.2. The cobas® 4800 Human Papillomavirus (HPV) Test is a qualitative in vitro test for the detection of Human Papillomavirus in patient specimens. The test utilises amplification of target DNA by the Polymerase Chain Reaction (PCR) and nucleic acid hybridisation for the detection of 14 high-risk (HR) HPV types in a single analysis. The test specifically identifies (types) HPV16 and HPV18 while concurrently detecting the rest of the high-risk types (31, 33, 35, 39, 45, 51, 52, 56, 58, 59, 66 and 68) at clinically relevant infection levels. The cobas® assay simultaneously tests for human beta-globin as an internal control of sufficient specimen cellularity. In addition, a positive and negative control specimen will be included in each run.

HPV testing will be performed with the liquid-based cytology (LBC) ThinPrep platform (PreservCyt) by the HSL laboratory. Samples will be prepared and processed following the Roche company guidelines.

The laboratory will record presence of human beta-globin, HPV result including HPV type (16/18 and other), although only HPV results without type will be reported to GPs and to women.

Results will be recorded in the usual NHS laboratory electronic LIMS database. Results will be reported from the laboratory to the GP practices using electronic links and automatically coded into EMIS Web if possible. Where electronic lab links are not available results will be sent via letter to the GP Laboratory Information System (LIMS).

The laboratory will stop analysing self-samples one month after the last kit has been sent out (including repeat kits for unavailable results). Women will be informed of this when they receive their kit.

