### **7.10 End of Trial**

The end of the active recruitment of the trial will be defined as either when a minimum of 10,000 kits have been returned or at 12 months after study start, whichever is earliest.

The trial will end once a minimum of 6 months of follow-up data (6 months from the last participant recruited) for women testing HPV positive on a self-sample have been received.

The Chief Investigator will inform the REC of the end of the trial within 90 days of its completion. A summary of the final research report will be sent to the REC within 12 months of the end of the trial

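### The extra contact for HPV-positive women without a follow-up test is dated to the end of recruitment, when some results may still be unreported; a short catch-up run would close the gap

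*Protocol*

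**What the plan says.** Section 7.5.2 (HPV Positive) describes a further safety net and gives its date and its target group in these words: "when the trial reaches the end of recruitment, all self-sample screen positive women who have not attended for a follow up test". The practice of each such woman is told about her and is the party "who will make one further attempt to contact the women to come for a follow up test". The practice identifies them with a pre-written search of its records, or the laboratory supplies the list.

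Section 7.10 (End of Trial) dates the trigger: "The end of the active recruitment of the trial will be defined as either when a minimum of 10,000 kits have been returned". The alternative trigger is 12 months after study start, and the earlier of the two counts. The same section says "The trial will end once a minimum of 6 months of follow-up data (6 months from the last participant recruited". That follow-up concerns the HPV-positive women.

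Two other sections imply different dates for the end of recruitment. Section 4.4 equates it with the return of the last self-sample. The long-term coverage row of section 3.2 counts its 13 months from the last kit sent or given.

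On the laboratory side, section 7.6.3.2 says "The laboratory will stop analysing self-samples one month after the last kit has been sent out (including repeat kits for unavailable results". Section 7.4 sets the reporting target: "The laboratory will aim to report HPV results (i.e. authorised report released to NHAIS) within 5 days of receiving a self-sample". It then sets one for the letter: "Women should receive their results letter within two weeks of returning a self-sample".

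Section 7.5.3 has a parallel GP search that "will identify all women with an unavailable self-sample result who either do not return a repeat". It also covers those with two consecutive unavailable results. It gives no date for that search.

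**The concern.** Section 7.5.2 offers the extra contact to all HPV-positive women without a follow-up test, but a search finds only positives already reported on the day it is run. If it is run on the section 7.10 date, some kits are still with women and some samples are in the post or in the laboratory. Women among them who later test positive and do not attend are not listed, and sections 7.5.2, 7.8 and 7.10 describe no later search. About 106 practices are expected to act on this instruction, and it does not say which meaning of the end of recruitment applies.

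At stake is one telephone call or text message to a small number of known HPV-positive women who were already overdue for screening. No endpoint definition, sample size or analysis is affected.

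**Working it through.** **Planned volumes reproduced (sections 9.1.1 and 9.1.2).**
- Mail-out kits: 106 × 20 × 9 = 19,080 (stated about 19,000). Returns: 19,000 × 15% = 2,850 (stated about 2,800).
- Opportunistic returns: 17,000 × 50% = 8,500 (as stated).

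**Monthly returns at full recruitment.** Mail-out 106 × 20 × 15% = 318; opportunistic 8,500 / 9 = 944; total 1,262.

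**When the trigger falls.** Assume that practice starts are spread evenly over months 0 to 6, so the mean start is month 3. After month 6, cumulative returns are 1,262 × (t − 3). Setting this to 10,000 gives t = 10,000 / 1,262 + 3 = 10.9 months. The 10,000 rule therefore comes before the 12-month rule, with all practices still recruiting.

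**Samples reported after a search on that date.** Return delays are assumed, because the protocol gives none.
- Low: mail-out only, delay 0.25 month, no laboratory queue: 318 × 0.25 = 80.
- High: mail-out delay 1 month, 318; opportunistic delay 0.25 month, 944 × 0.25 = 236; in the laboratory for 5 days, 1,262 × 5 / 30.4 = 208. Total 318 + 236 + 208 = 762.

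**Women affected.** The protocol gives no HPV positivity, so 10% to 20% is assumed. Non-attendance is 15% to 18%, from the 85% and 82% attendance cited in section 7.5.2.
- Low: 80 × 10% = 8 positives; 8 × 15% = 1.2 non-attenders.
- High: 762 × 20% = 152 positives; 152 × 18% = 27 non-attenders.

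As a check under cruder assumptions, spread 2,850 + 8,500 = 11,350 returns evenly over 9 months (1,261 a month). Let a quarter to all of one month's returns fall after the date: 315 to 1,261 samples. At 8% to 20% positivity that is 25 to 252 positives, and at 15% to 18% non-attendance about 4 to 45 women.

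**The same gap under each meaning of the end of recruitment.**

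| Meaning | Still unreported on that date |
|---|---|
| 10,000 returns or 12 months (7.10) | Kits still out, samples in transit, laboratory queue |
| Last kit sent or given (3.2) | About one month of returns plus the laboratory queue |
| Last self-sample returned (4.4) | About the 5-day reporting lag |

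**When a complete list becomes possible.** Count days from the last first-issue kit.
- No repeat kit: sample accepted to day 30; reported by 30 + 5 = day 35; letter by 30 + 14 = day 44.
- Repeat kit after insufficient DNA: letter by day 44; kit about 7 days later, day 51; laboratory closes 30 days after that, day 81; reported by day 86; letter by 81 + 14 = day 95.

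A run at 3.5 to 4 months (3.5 × 30.4 = 106 days; 4 × 30.4 = 122 days) comes after the last letter. It leaves 182 − 106 = 76 to 182 − 122 = 60 days of a 6-month follow-up. The section 7.5.3 search needs a similar date, because non-return of a repeat kit is known only after about day 81.

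**The case against.** The strongest reply is that the gap depends on which date is meant. Women join the trial by returning a sample (sections 7.3.2 and 7.3.4), so the last participant recruited in section 7.10 can be read as the last woman to return one, which agrees with section 4.4. On that reading only results from the last few days are pending. This stands, and it is why the point is minor. It does not remove the point: section 7.10 gives an explicit definition, and section 7.5.2 does not say that another one applies.

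A reader might infer that the protocol prescribes a single search. It does not. It limits contacts to one further attempt per woman and states no number of searches; what can be said is that no later one is described.

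A reader might also infer that late positives are left without follow-up. The documents do not support that. Section 7.5.2 gives every HPV-positive woman a results letter, early recall at 3 months and two reminder letters, none tied to the end of recruitment. For the latest positives, most of that pathway is still ahead.

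Finally, the counts rest on assumed positivity, return delays and start dates. The high case also allows a delay for opportunistic kits, although section 7.2.2 encourages collection at the practice. That stands too.

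**Conclusion.** The point holds in a limited form. A search on the date defined in section 7.10 would miss HPV-positive women whose results are reported later, so the extra contact would not reach all the women section 7.5.2 says it covers. The size is roughly one to a few tens of non-attenders (1 to 27 under one set of assumptions, 4 to 45 under another). On section 4.4's meaning the gap is about 5 days of reporting. The counts depend on the assumptions; on the section 7.10 definition, the order of events does not. The women affected lose only the additional contact. Severity is minor. It is worth correcting because the remedy is cheap and fits inside follow-up that is already planned.

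**What to change.** In section 7.5.2, keep the run at the end of recruitment and add a sentence along these lines: one catch-up run will be made, together with the search in section 7.5.3, after the laboratory's last result has been reported and its results letter sent, and before the 6-month clinical follow-up closes; it is limited to HPV-positive women without a follow-up test who were not contacted at the first run. About 3.5 to 4 months after the last first-issue kit is suitable. The restriction keeps to one further attempt per woman. Tying the run to the laboratory's last result means that the differing meanings of the end of recruitment no longer matter for this safety net.

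Cost: one sentence and one more short list for each of about 106 practices, from the search or laboratory list that section 7.5.2 already allows. There are two downsides. The call prompts these late positives inside the 6-month window of the compliance endpoint, as the existing attempt already does for recent positives. For the latest of them it may also precede the 3-month recall, but section 7.5.2 allows the follow-up test to be taken immediately after a positive result.

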### **7.5.3 Unavailable due to insufficient DNA**

Women who return a sample that has insufficient DNA (i.e. human beta globin not detected) to produce a viable result will be asked to repeat the self-sample in their results letter sent by CSAS. This will trigger a repeat kit to be made available to them within approximately 1 week of their results letter being sent. Based on a previous study we expect this to be rare (2%).(16)

If the repeat self-sample is also unavailable due to insufficient DNA, women will be advised (in their results letter sent by CSAS) to attend their GP practice for a conventional cervical screening test (collected by a nurse or doctor). This approach has been chosen because women who return a repeat kit indicates that they are highly motivated to be screened. There are no clinical safety concerns as two consecutive unavailable due to insufficient DNA results on a self-sample indicates poor sample-taking, not higher risk of having cervical abnormalities.

Unavailable results due to insufficient DNA will not elicit an action in NHAIS and their NTDD will remain unchanged.

As with women testing HPV positive, women who have an unavailable test result (due to insufficient DNA) will be safety-netted at their GP practice. A pre-written search of EMIS web (electronic patient record software) will identify all women with an unavailable self-sample result who either do not return a repeat (2nd sample) or who test unavailable on two consecutive samples. GP practices will be asked to contact these women (by letter, telephone call or text message) to invite them to come for a conventional screening test.

### 7.5.4 Invalid samples

Invalid samples arriving at the laboratory will not be analysed. The sample details will be recorded on the central laboratory LIMS database but will not be reported back to the NHAIS database.

Samples will be considered to be “invalid” for analysis if they:

1. arrive >14 days after the date the sample has been taken (as recorded on the sample tube and lab request/consent form; or
2. do not meet the minimum required information on the sample tube and/or lab request/consent form to meet NHSCSP requirements for valid samples or
3. are returned by women who are ineligible.

As invalid samples will not be analysed or reported to NHAIS, a letter cannot be sent by CSAS. Therefore, the print company (CFH Docmail) will send a letter to women who return an invalid sample, informing them of this, and advising them that they will either receive a repeat kit or should book for a clinician-taken sample at their GP practice (as appropriate). The central laboratory will securely send (via secure file transfer protocol (SFTP)) the necessary details to issue these letters and repeat kits to CFH Docmail (NHS number, full name, date of birth, postal address, GP practice code, study ID (encrypted NHS number)). Results will be sent to the GP practices in the usual way (electronic lab links). The trial team at King's will receive the list of encrypted NHS numbers with date of invalid result in order to ensure sufficient oversight for this process.

Samples returned by women who are ineligible (i.e. women who are not  $\geq 6$  months overdue cervical screening) may arise if they receive a kit and are screened by conventional screening or self-sample or if they have received a kit in error. The central laboratory will contact the women's GP practice to inform them that the sample is invalid and will therefore not be analysed or reported to NHAIS. The GP practice will in turn, contact the woman to inform her that her sample was not analysed because she is not eligible.

Detailed instructions for the handling of invalid samples by the laboratory will be included in the YouScreen Laboratory Manual, in accordance with current NHSCSP guidelines.

**Table 1 Proposed codes for recording self-samples in NHAIS**

| Self-Sample HPV result             | HPV primary screening flag | Infection Code | Result Code | Action Code | Call/recall Action in NHAIS                                                                                                                                                                                  |
|------------------------------------|----------------------------|----------------|-------------|-------------|--------------------------------------------------------------------------------------------------------------------------------------------------------------------------------------------------------------|
| HPV Negative                       | S                          | 0              | X           | A           | Reset Next Test Due Date (NTDD) using the standard call/recall protocol.                                                                                                                                     |
| HPV Positive                       | S                          | 9              | X           | R (3)       | Reset NTDD with an early recall of 3m (will restart the call/recall cycle and automatically add them to the PNL list that is sent to GPs. NTDD would be reset again if the women had standard screening test |
| HPV unavailable (insufficient DNA) | S                          | U              | X           | H           | NTDD unchanged.                                                                                                                                                                                              |

### 7.5.5 Pregnant women

Although pregnant women will be advised against taking part in the trial it is highly likely that several will return a self-sample. A kit may be sent in the mailout offer to a woman who is pregnant because pregnancy is not recorded on the NHAIS database.

This also may be because women may not realise they are pregnant at the time of sampling or because they do not see the text advising against it in the participant information booklet or instructions..

There are no safety issues with a pregnant woman using a vaginal swab to self-collect, even if she touches her cervix or if the swab breaks (the broken end would be at the vagina entrance, not near

the cervix). In addition, cervical screening is not contraindicated in pregnancy. However, the NHSCSP recommends pregnant women to defer their cervical screening until 12 weeks post-partum. Therefore, if a pregnant woman returns a self-sample in the trial, her data will be included. Women with HPV negative self-sample results will be treated in the same way as set out above. HPV positive women on a self-sample should be followed up with a clinician-taken sample for cervical screening. If the GP/nurse at the practice feel unable to do this, then they should refer the woman to a cytology clinic within the local colposcopy service. Experienced clinical staff within colposcopy are more used to assessing a pregnant cervix.

**Figure 4 Clinical management for self-sampling**

[figure not shown]

## 7.6 Central Laboratory Process (HPV Testing)

All valid self-samples from the women will be analysed for presence of high-risk HPV by the central laboratory in London contracted to deliver all testing for cervical screening in London as part of the NHS cervical screening programme. This is currently the Health Services Laboratories (HSL) at [name], however may change if there are changes within the NHSCSP. HSL will perform activities according to the standards set out in the cervical screening programme guidelines, which will be further defined in a YouScreen Laboratory Manual and HSL standard operating procedures developed for the purpose of the YouScreen trial. HSL, as the contracted London laboratory for the NHSCSP have existing access to NHAIS data.

### 7.6.1 Sample collection and transfer

Women who accept a self-sampling kit in their GP practice (opportunistic) will have the option of collecting their sample in the clinic bathroom or at home. Samples collected at the GP practice will be picked up daily via the usual NHS laboratory sample collection services for delivery to the central laboratory. If this is not feasible, samples will be posted daily to the central laboratory by the GP practice staff using pre-addressed freepost envelopes provided with the self-sampling kit.

Women who are sent kits via direct mail-out will collect their sample at home. All samples collected by women at home will be posted dry under ambient conditions to the central laboratory for analysis (using a freepost, pre-addressed UN3373 compliant box or envelope that will be provided with the kit). Women will be advised to post the sample within 5 days of taking it. Samples that are returned more than 14 days after sample collection will be rejected by the laboratory.

All self-sampling kits will contain freepost envelopes pre-addressed to the central laboratory at Health Services Laboratories, [name].

## **7.6.2 Sample labelling**

### **7.6.2.1 Opportunistically offered kits**

Sample tubes will be pre-labelled with a unique kit number. The GP/nurse/HCA offering the kit will write 3 identifiers (e.g. full name (first and last name counts as two identifiers, date of birth (DOB)) on the label. Women will be instructed to write the date the sample was taken on the sample tube and on the lab request/consent form. The date the sample was taken should only be entered after the sample has been taken to avoid inaccurate sample dates being received (the date sample taken will inform the NTDD in call/recall, and acceptable sample validity for analysis).

### **7.6.2.2 Direct mail-out**

Sample tubes will be pre-labelled with a unique kit number, the woman's full name, NHS number, Date of Birth and GP National Code. If pre-labelled tubes are not possible, a peel and stick label with these details pre-populated will be included in the kit for the woman to attach to the tube. Women will be instructed to write the date the sample was taken on the sample tube and on the lab request/consent form.

